8.1 Methods for Measurement of Endpoints for Clinical Efficacy

Composite Relapse Endpoint:

- - BMI Decrease: Measured at baseline, 5 weeks, and 6 months using calibrated equipment and standardized protocols.
  - Hospitalization Data: Collected through patient reports and confirmed by medical records.
  - Symptom Deterioration: Assessed using validated tools such as the EDE-Q 6.0 and clinical interviews conducted by trained staff.
  - Clinical Intervention Use: Recorded in patient files, including initiation of new treatments during follow-up.

Changes in AN symptom (EDE-Q 6.0).

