4.4 Secondary Endpoints

- Time to **Relapse:**

Defined as a composite outcome during the follow-up period, consisting of:

1. **≥7 % decrease in BMI** compared to post-hospitalization baseline BMI.

Rationale for 7 %: A 7% decrease in BMI reflects a significant deviation from expected weight gain in patients starting at a minimum BMI of 16, signaling potential relapse.

1. **Re-hospitalization for anorexia nervosa-related complications** (e.g., significant weight loss, medical instability). Data of hospitalization will be collected from hospital journal registers.
2. **Initiation of additional intensive psychiatric or nutritional interventions**, including day-patient or inpatient programs. Data of additional interventions will be collected from hospital journal registers.
3. **Self-reported significant deterioration in eating disorder symptoms** (e.g., severe food restriction, purging) as assessed by validated scales such as the Eating Disorder Examination Questionnaire 6.0 (EDE-Q 6.0).

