**5.2 Procedures and Schedule of Assessment**

All procedures will be conducted at the University Hospital for Psychiatry, [name], except the fMRI assessments which are performed at the The National 7T Facility in Lund. All assessments will be carried out by qualified personnel appointed by the principal investigator, including medical doctors, nurses, and psychologists. The National 7T Facility will appoint qualified personnel for fMRI assessment.

The duration of the entire trial is from the first screening of the first patient to the last follow up of the last patient. For each patient participant, the duration of the trial is from the screening to the last follow up at week 52 (12 month).

Patient rehospitalization and additional interventions data are collected in patient journal registers.

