**All concomitant medications will be carefully documented and considered in the interpretation of clinical outcomes.**

The following psychiatric medications are prohibited in participants receiving psilocybin due to known or potential pharmacodynamic interactions and risk of attenuated psychedelic effects or adverse reactions:

•Monoamine oxidase inhibitors (MAOIs)

•Tricyclic antidepressants (TCAs)

•Benzodiazepines ≤ 2 mg lorazepam equivalents per day (must not be taken within 12 hours prior to psilocybin administration)

•Antipsychotics

•Lithium

Participants will undergo a thorough medication review during screening to identify potential pharmacological interactions. Medications with prohibited serotonergic activity require washout periods of 2–4 weeks before psilocybin dosing according to clinical practise guidelines.

- Participants who cannot safely discontinue contraindicated medications will not be included in the study.

- The washout will primarily be monitored by phone and a medical doctor within the research team appointed by the principal investigator, with in-person visits if needed. Participants who exceed the 8-week limit without dosing will be re-evaluated for eligibility by the principal investigator. The time from screening to first dosing shall not exceed 8 weeks regardless of washout status.

- Psychotherapy and other non-pharmacological treatments will be allowed throughout the study period as TAU if not deemed an exclusion criterion. Temporary daycare after discharge will be considered part of TAU rather than non-pharmacological treatment.

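### For time to relapse, Section 8.1 finds admissions through patient report where 4.4 and 5.2 use registers, and it describes the intervention component without the 4.4 intensity qualifier

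*Protocol*

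**What the plan says.** Section 4.4 lists time to relapse first among the secondary endpoints and defines it as a composite. Two components concern use of care. One is re-hospitalisation for complications of anorexia nervosa. The other is "Initiation of additional intensive psychiatric or nutritional interventions", with day-patient and inpatient programmes named as included. Section 4.4 gives the source for each: "Data of hospitalization will be collected from hospital journal registers", and "Data of additional interventions will be collected from hospital journal registers". Section 5.2 repeats this: "Patient rehospitalization and additional interventions data are collected in patient journal registers".

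Section 8.1 describes how the same composite is measured. Hospitalisation data are "Collected through patient reports and confirmed by medical records". Clinical intervention use is "Recorded in patient files, including initiation of new treatments during follow-up". Section 8.1 does not refer back to 4.4 for either item.

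Section 7.3 bears on the second component: "Psychotherapy and other non-pharmacological treatments will be allowed throughout the study period as TAU if not deemed an exclusion criterion". The sentence after it places temporary day care following discharge within TAU.

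**The concern.** The protocol states the source of admission data in three places, and one of them disagrees. A register search looks for admissions in everyone. A route that starts with the patient and then checks the record looks only for admissions that someone mentioned. A participant who stops attending has little occasion to mention one, and may have stopped because the illness worsened. Under the second route such a person may be carried as relapse-free, or censored, when the event has happened. Participants know their allocation, so attendance and willingness to report may differ between arms, and the loss need not be balanced.

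The intervention component raises a smaller question. Someone coding events from 8.1 alone would find a reference to new treatments and no intensity threshold. Section 7.3 allows non-pharmacological treatment throughout, so non-intensive treatments can start in either arm without signalling relapse. The coder should not have to infer that 4.4 governs.

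**Working it through.** No arithmetic applies. The protocol gives no relapse rate, event count or hazard ratio for this endpoint, and Section 10.4 says that no formal power calculation was made. The check is a comparison of the sections.

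**1. Admissions: which cases differ between the two routes.**

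- Reported by the patient and in the register: found under 4.4/5.2 and under 8.1.
- Not reported, but in the register: found under 4.4/5.2, missed under 8.1.
- Reported, but not in the register (care elsewhere): missed under 4.4/5.2, found under 8.1 if another medical record confirms it.
- Neither reported nor in the register: missed under both.

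The routes differ in the second and third cases. Confirmation in the record, as 8.1 requires, removes false reports but does not recover unreported admissions.

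**2. Whether the second case is realistic here.** Section 6.4 names repeated missed visits as a possible reason to stop dosing, keeps such participants in follow-up, and ends participation only on withdrawal of consent. Section 10.1 puts every randomised participant in the intention-to-treat analysis. The protocol therefore expects some poor attenders to remain in the analysis. BMI and the EDE-Q are collected at study visits, so for a participant who misses visits the two care-use components are the ones that can still be found, provided they come from registers.

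**3. Whether adverse-event reporting closes the gap.** Inpatient admission is a serious adverse event under 9.1, and 9.3 collects such events to 12 months. But 8.2 describes collection as spontaneous reporting by the participant or clinician at in-person visits, and 9.3 as recording at contacts with the participant. This route also depends on contact.

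**4. Whether the arms could differ.** Section 5.1 describes an open-label design. Section 5.2 gives the psilocybin arm preparation, dosing and integration visits, which are extra occasions to report. The direction and size of any net difference cannot be derived from the document.

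**5. Intervention component: whether 8.1 changes the definition.** The qualifiers in 4.4, set against 8.1:

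- BMI: a fall of at least 7% in 4.4; a BMI decrease without a threshold in 8.1.
- Admission: related to anorexia nervosa in 4.4; hospitalisation without that limit in 8.1.
- Symptoms: significant deterioration in 4.4; deterioration in 8.1.
- Interventions: additional and intensive in 4.4; new treatments in 8.1.

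The qualifier is absent from all four. That marks 8.1 as a list of what is captured, with 4.4 as the definition. The fourth item still stands apart a little: 8.1 does more than shorten the label, since it names the start of new treatments as an example of what is recorded.

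**6. A related conflict.** Section 4.4 counts starting a day-patient programme as relapse. Section 7.3 treats temporary day care after discharge as TAU. A participant who enters day care after discharge during follow-up could be placed under either.

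**The case against.** The strongest reply is that 8.1 is a methods section and does not override 4.4. Read together, 4.4, 5.2 and 8.1 could mean a register search plus patient report, which is close to what is asked for here. Both routes end in the medical record, 8.1 does not withdraw the register source, and adjudication detail is commonly left to a statistical analysis plan.

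Much of this stands. A reader might infer that admissions in non-attenders are never looked for. The documents do not support that, because 4.4 and 5.2 both provide for registers. A reader might also infer that under 8.1 a new outpatient psychotherapy or antidepressant is a relapse event. Section 8.1 says only that new treatments are recorded, and the same reading applied to BMI would make any fall a relapse. That the two sections count different patients is possible but not established.

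What does not fall away is the stated source. The protocol names the first source of admission data differently in 8.1 than in 4.4 and 5.2, and does not say that the two are to be combined. This is an inconsistency in the text, not a detail left to a later plan.

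**Conclusion.** The point holds in a limited form. The source of admission data is inconsistent: registers in 4.4 and 5.2, patient report with confirmation in 8.1. If 8.1 is the rule followed, unreported admissions can be lost, and possibly unequally between arms. The intervention wording in 8.1 is looser than 4.4 and open to a broader reading, but it does not redefine relapse. The day-patient wording in 4.4 and the day-care wording in 7.3 also conflict and must be reconciled.

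No size can be attached. It is tempting to assume relapse rates and show a diluted risk ratio or lost power. Such rates have no source in the protocol, the exercise would rest on counting every new treatment as relapse, and a comparison of proportions does not measure a time-to-event endpoint. Severity is low: this is one secondary endpoint in a pilot whose primary aim is safety and whose Section 5.1 acknowledges limited power for between-group differences. The conclusion assumes that some participants miss visits while remaining in follow-up, which 6.4 anticipates, and that the registers hold most relevant admissions, which the protocol does not document.

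**What to change.** In Section 8.1:

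- State that admissions and intensive interventions are identified by the register search already planned in 4.4 and 5.2, for every randomised participant who has not withdrawn consent and regardless of visit attendance. Keep patient report as a supplement for care outside the registers.
- State that only interventions meeting the 4.4 definition count as relapse, and that other new treatments are recorded only. Refer to the definition as it stands: day-patient and inpatient programmes are named there as included, not as the only qualifying forms.
- When making these edits, reconcile the day-patient component in 4.4 with the treatment of temporary day care after discharge in 7.3, so that each such episode has one classification. Which way to settle it is for the sponsor.

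The cost is a few sentences. Register access is already planned, and no visit, assessment or participant is added. The change is best made before relapse events are classified, because allocation is known to those who will classify them.

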8.2 Methods for Measurement of Endpoints for Clinical Safety

Continuous clinical safety monitoring will be performed by licensed healthcare professionals at Lund University Hospital throughout the trial, from baseline to the final 12-month follow-up. The safety evaluations cover physical, biochemical, and psychological parameters relevant to psilocybin administration.

For a complete list and overview, please visit the Schedule of Assessments attached to the protocol.

- **Hepatic and renal function:** Blood samples will be collected to assess creatinine, albumin, PK-INR, ALAT, ASAT, GT, ALP, and bilirubin levels. These assessments will occur during screening, at baseline (Week 0), after each psilocybin dosing, at the primary endpoint, and at the 6-month follow-up (Week 24).
- **Glucose:**Measured at the same time points as above – during screening, baseline, after each dosing, at the primary endpoint, and the 6-month follow-up. Additionally, glucose levels will be assessed at 9- and 12-month follow-up visits.
- **Urine toxicology (U-tox):** Drug use screening will be performed at baseline, and again at 6-, 9-, and 12-month follow-ups.
- **Cardiovascular parameters (ECG, blood pressure, pulse):** These will be measured at screening, baseline, after each dosing session, during the first integration sessions (1 day post-dosing), and at all subsequent follow-ups.
- **Assessment of suicidality and psychiatric safety:** Suicidality will be assessed using the Columbia-Suicide Severity Rating Scale (C-SSRS) at baseline, after each psilocybin session, during integration, and at all follow-ups. Psychiatric symptoms will be monitored using the Brief Psychiatric Rating Scale – Extended (BPRS+).
- **Mental health symptoms:** Self-report instruments including the PHQ-9 (depression), GAD-7 (anxiety), and other measures will be completed at baseline, at each integration visit, at the primary endpoint, and at the 12-month follow-up.
- **Adverse Events (AE/SAE):** Spontaneously reported by participant patients or by clinician at all in-person visits from first dosing onwards, including all integration and follow-up assessments.

All data will be collected under Good Clinical Practice (GCP) conditions and entered the electronic case report form (eCRF) by trained personnel.

9. Handling of Adverse Events

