**Rationale for dosing interval:**

Several clinical trials have consistently demonstrated that administering two doses of psilocybin spaced 2 to 4 weeks apart is both safe and therapeutically appropriate when delivered under professional supervision with structured integration support (Bogenschutz et al., 2022; Carhart-Harris et al., 2021; Davis et al., 2021; Garcia-Romeu et al., 2015; Gukasyan et al., 2022). These dosing intervals are grounded in empirical findings from multiple populations and indications. For instance, Carhart-Harris et al. (2021) administered two 25 mg doses of psilocybin three weeks apart to 59 individuals with depression, reporting no serious adverse events (SAEs) and only transient effects such as headache and nausea. Garcia-Romeu et al. (2015) conducted a feasibility study in 15 smokers, administering 20 mg/70 kg and 30 mg/70 kg doses spaced by approximately two weeks; again, no SAEs were reported, and the design highlighted psychological integration. Davis et al. (2021) employed a two-week interval between doses in 24 patients with depression. Finally, Bogenschutz et al. (2022) studied 93 individuals with alcohol use disorder, spacing two 25 mg doses four weeks apart, with no serious adverse drug reactions noted. Collectively, these studies support the 4 week interval as an evidence-based standard that balances therapeutic efficacy with participant safety.

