**Screening Phase**

A brief telephone pre-screening is performed before the screening visit to avoid unnecessary visits for patients. This is conducted following verbal permission to access medical records and a verbal consent to a short pre-screening assessment to determine whether participants may qualify for full screening. Screening includes psychiatric and medical history, inclusion/exclusion criteria assessment, safety blood tests (glucose, liver, kidney), and, when clinically indicated additional laboratory tests to exclude common medical conditions and support eligibility assessment, ECG, informed consent (with a 2-week consideration period), pregnancy test and urine toxicology (U-tox). The time from screening to the first psilocybin dosing session must not exceed 8 weeks.

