**Preparation Phase**

- Preparation Session 1 & Baseline Assessment (Week 0): Psychoeducation about psilocybin, breathing and relaxation techniques, rapport-building with therapists, and discussion of expectations and concerns.
  Includes full baseline assessments (list provided as attachment to protocol:
  - Expectation of Treatment Scale (ETS-BF)
  - Readiness and Motivation Questionnaire (RMQ)
  - General Change Mechanisms Questionnaire (GCMQ)
  - Patient Health Questionnaire (PHQ-9)
  - Generalized Anxiety Disorder scale (GAD-7)
  - Eating Disorder Examination Questionnaire (EDE-Q )
  - Columbia-Suicide Severity Rating Scale (C-SSRS)
  - Brief Psychiatric Rating Scale – Extended (BPRS+)
  - Satisfaction With Life Scale (SWLS)
  - Positive and Negative Affect Schedule (PANAS)
  - Harmony in Life Scale (HILS)
  - Ten Item Personality Inventory (TIPI)
  - Honesty-Humility Scale (HH)EGON
- Visual size estimation (EGON)

Vital signs, ECG, blood glucose, urine drug screening, pregnancy test, fMRI, BMI and blood sampling for BDNF and safety labs are also conducted.

Preparation Session 2 (Week 1): Conducted 7–10 days after Preparation 1, and 2–3 days before psilocybin dosing.

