**Dosing and Integration Phase**

Dosing Session 1 (Week 1): Psilocybin 25 mg under therapeutic support with ECG, blood glucose and blood pressure/pulse monitoring.

Integration Session 1 (Day after Dosing 1): Reflection, fMRI, blood sampling (including glucose, liver, kidney, BDNF), and reassessments with RMQ, GCMQ, PHQ-9, GAD-7, C-SSRS, BPRS+, SWLS, PANAS, HILS, TIPI, ECG and blood pressure/pulse. Psychedelic Experience related scales; Altered States of Consciousness Rating Scale (5D-ASC), Mystical Experience Questionnaire (MEQ-4), Meaningful Life Experience Rating (MLE).

Integration Session 2 (Week 2): Continued psychological integration support.

Integration Session 3 (Week 3): Summary of first dosing experience and preparation for second dosing. A pregnancy test is performed.

Dosing Session 2 (Week 4): Second psilocybin 25 mg administration under identical conditions as first dosing session.

Integration Session 4 (Day after Dosing 2): Reflection, blood sampling (including glucose, liver, kidney, BDNF), and reassessments with RMQ, GCMQ, PHQ-9, GAD-7, C-SSRS, BPRS+, SWLS, PANAS, HILS, TIPI, ECG and blood pressure/pulse. Psychedelic Experience related scales; Altered States of Consciousness Rating Scale (5D-ASC), Mystical Experience Questionnaire (MEQ-4), Meaningful Life Experience Rating (MLE).

Integration Session 5 (Week 5): Final integration session and preparation for long-term follow-up.

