**Primary Endpoint Week 9**

Includes full safety and outcome evaluations:
- fMRI

- blood sampling (including glucose, liver, kidney, glucose, BDNF)
- Vital signs, ECG, U-tox

- BMI
- AE/SAE monitoring
- Readiness and Motivation Questionnaire (RMQ)
- General Change Mechanisms Questionnaire (GCMQ)
- Patient Health Questionnaire (PHQ-9)
- Generalized Anxiety Disorder scale (GAD-7)
- Eating Disorder Examination Questionnaire (EDE-Q)
- Columbia-Suicide Severity Rating Scale (C-SSRS)
- Brief Psychiatric Rating Scale – Extended (BPRS+)
- Satisfaction With Life Scale (SWLS)
- Positive and Negative Affect Schedule (PANAS)
- Harmony in Life Scale (HILS)
- Ten Item Personality Inventory (TIPI)
- Honesty-Humility Scale (HH)

- Visual size estimation (EGON)

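### Section 8.2 lists fewer urine drug tests than section 5.2, and neither lists one between baseline and the second psilocybin dose

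*Protocol*

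**What the plan says.** The urine toxicology bullet in Protocol section 8.2 reads: "Drug use screening will be performed at baseline, and again at 6-, 9-, and 12-month follow-ups".

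Section 5.2 goes through the visits one by one:

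- The Screening Phase includes "pregnancy test and urine toxicology (U-tox").
- At Preparation Session 1 (week 0, baseline): "Vital signs, ECG, blood glucose, urine drug screening, pregnancy test, fMRI, BMI and blood sampling for BDNF and safety labs are also conducted".
- The week 9 visit includes "Vital signs, ECG, U-tox". Urine toxicology is listed again at months 3, 4, 5, 6, 9 and 12.
- The Dosing and Integration Phase lists ECG, glucose, blood pressure and pulse, blood samples, rating scales and fMRI, but no drug test. Integration Session 3 (week 3) is described as: "Summary of first dosing experience and preparation for second dosing. A pregnancy test is performed". The second dose is described as: "Dosing Session 2 (Week 4): Second psilocybin 25 mg administration under identical conditions as first dosing session".

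Section 6.2 makes a positive drug test an exclusion criterion. Section 6.4 gives the emergence or discovery of an exclusion criterion after inclusion as a possible reason to withhold the first or second dose, with pregnancy as one of its examples. Section 8.2 refers to an attached Schedule of Assessments for the complete list. That attachment is not part of the visible text.

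**The concern.** There are two separate problems.

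First, the two sections give different test schedules. The short list in 8.2 does not look like deliberate shorthand. In the same section the liver and kidney bullet and the glucose bullet name screening and the primary endpoint, and the cardiovascular bullet names screening and every later follow-up. The urine toxicology bullet names neither screening nor week 9, and skips months 3 to 5.

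Second, the protocol has a rule that can stop dose 2, but the visible text lists no test that would trigger it for drug use starting after baseline. For pregnancy, which falls under the same rule, it does: section 9.8.2 and Integration Session 3 both provide a repeat test. For drug use, only self-report and clinical contact remain until after both doses.

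What is at stake is participant safety at dose 2. A participant who began using drugs after baseline could be given 25 mg of psilocybin without a check. A minor further point is that an acute event after dose 2 might be graded for relatedness without a recent drug test at hand.

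**Working it through.** The protocol gives no figure of its own to reproduce. The check is a count of listed tests and a calendar.

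**Count of listed urine drug tests**

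| Time point | 5.2 | 8.2 |
|---|---|---|
| Screening | yes | no |
| Baseline (week 0) | yes | yes |
| Preparation 2, dosing 1, integration 1 to 3, dosing 2 | no | no |
| Integration 4 and 5 | no | no |
| Week 9 | yes | no |
| Months 3, 4, 5 | yes (3 visits) | no |
| Month 6 | yes | yes |
| Month 9 | yes | yes |
| Month 12 | yes | yes |
| Total | 9 | 4 |

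Difference: 9 − 4 = 5 (screening, week 9, months 3, 4 and 5). All four time points in 8.2 are among the nine in 5.2. Nine is the number of visits in 5.2 that list the test, not the number of visits in 5.2.

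**Time from the last listed test to each dose**, with baseline (Preparation Session 1) as day 0

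- Preparation Session 2 is "Conducted 7–10 days after Preparation 1, and 2–3 days before psilocybin dosing". It therefore falls on day 7 to 10.
- Dose 1 falls on day 7 + 2 = 9 at the earliest and 10 + 3 = 13 at the latest.
- Dose 2, reading A: taking the Week 4 label in 5.2 as four full weeks after baseline, 4 × 7 = day 28.
- Dose 2, reading B: the dosing-interval rationale says "Collectively, these studies support the 4 week interval as an evidence-based standard". Counting four weeks from dose 1 gives 9 + 28 = day 37 to 13 + 28 = day 41.

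The last listed drug test before dose 2 is the baseline test, so the gap is 28 days (A) or 37 to 41 days (B). Dose 1 comes 9 to 13 days after baseline and is preceded by two tests, at screening and at baseline.

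**Effect of a test at Integration Session 3**

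By the week labels, week 4 − week 3 = 1 week, so the gap falls from 28 days to about 7. If dose 2 follows reading B while Session 3 stays at week 3 (3 × 7 = day 21), the gap is 37 − 21 = 16 to 41 − 21 = 20 days. Session 3 should therefore move with dose 2.

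**The case against.** The strongest objection is that section 8.2 itself names the attached Schedule of Assessments as the complete list, and that Schedule cannot be seen. It may contain a test before dose 2. This stands, and it makes the second part of the point conditional. It does not remove the first part, because 5.2 and 8.2 give different lists whatever the Schedule says.

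It can also be said that the conflict is mild. The 8.2 list is a subset of the 5.2 list, it does not claim to be exhaustive, and a site that follows 5.2 visit by visit will do all nine tests. That is fair as to the practical harm, but the bullet still needs correcting.

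A third objection is that section 6.4 only says what reasons for stopping may include and does not promise to re-test every exclusion criterion. Participants with substance use disorder or any lifetime psychedelic use are excluded, each participant is tested twice at entry, and staff see them several times before dose 2. This lowers the likely risk. It does not explain why pregnancy is re-checked before dose 2 and drug use is not.

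Some stronger readings should be resisted:

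- A reader might infer that the safety results are compromised. The primary endpoint counts adverse events whatever their cause, so its incidence is unaffected. Relatedness under 9.2 rests on the available evidence and refers to underlying disease and other medications, and nothing prevents a test after an acute event. The effect on relatedness is minor.
- A reader might measure the exposure by the whole interval from baseline to the next listed test. Most of that interval lies after dose 2, and a later test cannot make dose 2 safer.
- A reader might attach a firm number of second doses. The protocol targets at least 20 participants with at least one dose, and switching by control participants is optional and depends on the safety committee, so any count of second doses is an assumption.

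**Conclusion.** The point holds in two parts of different strength.

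The conflict between sections 5.2 and 8.2 is certain on the text: five time points appear in one list and not in the other.

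The absence of a drug test between baseline and dose 2 holds for the visible text of both sections, with a gap of 28 days or 37 to 41 days depending on how the dose 2 date is read. It rests on the assumption that the attached Schedule of Assessments lists no such test. If it does list one, what remains is a correction to 5.2 and 8.2.

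This is a consistency error together with a cheap safety improvement, not a threat to the trial's validity. The protocol gives no basis for estimating how often drug use would start in that interval.

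**What to change.** 1. Align the urine toxicology bullet in 8.2 with 5.2 and with the attached Schedule of Assessments.
2. Check whether that Schedule already lists a drug test before dose 2. If it does, correct only 5.2 and 8.2 to match.
3. If it does not, add a urine drug test at Integration Session 3 alongside the pregnancy test, read before dose 2 is given, and keep that session in the week before dose 2.
4. State in 6.4 that a positive result not explained by a permitted prescribed medicine postpones or cancels the dose.
5. Apply the same test and rule to control participants who switch under section 7.4.

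The cost is one urine test per participant before dose 2 and an occasional postponed dose. No visit is added, and participants of childbearing potential already give urine for the pregnancy test before dose 2.
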